## Abstract

**Introduction:**

Men in sub-Saharan Africa are less likely than women to initiate antiretroviral therapy (ART) and more likely to have longer cycles of disengagement from ART programmes. Treatment interventions that meet the unique needs of men are needed, but they must be scalable. We will test the impact of various interventions on 6-month retention in ART programmes among men living with HIV who are not currently engaged in care (never initiated ART and ART clients with treatment interruption).

**Methods and analysis:**

We will conduct a programmatic, individually randomised, non-blinded, controlled trial. ‘Non-engaged’ men will be randomised 1:1:1 to either a low-intensity, high-intensity or stepped arm. The low-intensity intervention includes one-time male-specific counseling+facility navigation only. The high-intensity intervention offers immediate outside-facility ART initiation+male-specific counselling+facility navigation for follow-up ART visits. In the stepped arm, intervention activities build in intensity over time for those who do not re-engage in care with the following steps: (1) one-time male-specific counselling+facility navigation→(2) ongoing male mentorship+facility navigation→(3) outside-facility ART initiation+male-specific counselling+facility navigation for follow-up ART visits. Our primary outcome is 6-month retention in care. Secondary outcomes include cost-effectiveness and rates of adverse events. The primary analysis will be intention to treat with all eligible men in the denominator and all men retained in care at 6 months in the numerator. The proportions achieving the primary outcome will be compared with a risk ratio, corresponding 95% CI and p value computed using binomial regression accounting for clustering at facility level.

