### Analysis plan

Data analysis will be conducted in R: A Language and Environment for Statistical Computing (R Foundation for Statistical Computing). We will use the Consolidated Standards of Reporting Trials standards for reporting trial outcomes.^42^ Using an intention-to-treat analysis, all randomised men will be included in the analysis of the primary outcome; men with missing outcomes due to loss to follow-up will be treated as outcome failures. We will calculate descriptive statistics, including mean, SD, range and frequency distributions for the demographic characteristics and study outcomes by study arm. The primary outcome and all other binary outcomes will be analysed by logistic regression models with age, marital status, healthcare facility and other key sociodemographic variables included as covariates. The intervention effects will be tested by Wald tests of the relevant regression parameters. The hypotheses of no difference between the stepped arm and the low/high-intensity arm will be rejected if the p value is smaller than 0.025 (Bonferroni adjustment). CIs for ORs comparing the stepped arm with the low-intensity and high-intensity arms with coverage probabilities 0.975 will be calculated by profile likelihood methods. Due to the Bonferroni adjustment, the simultaneous coverage probability of both intervals will be at least 0.95. To address the secondary objectives, more elaborate logistic regression models will be built for each of the binary outcomes with available individual-level, community-level and facility-level factors included as covariates in addition to the intervention status.

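### The abstract and the Analysis plan section fix two different primary analyses (risk ratio with 95% CI versus adjusted odds ratio at 0.025 with 97.5% CI), and nothing says which prevails

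*Protocol article*

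**What the plan says.** The abstract (Methods and analysis) describes the primary analysis as "intention to treat with all eligible men in the denominator". It says the proportions retained will be "compared with a risk ratio, corresponding 95% CI and p value computed using binomial regression accounting for clustering at facility level". It names no covariates, no multiplicity adjustment and no significance threshold.

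The Analysis plan section states that "all randomised men will be included in the analysis of the primary outcome", with missing outcomes due to loss to follow-up counted as failures. Binary outcomes, the primary one included, are to be "analysed by logistic regression models with age, marital status, healthcare facility and other key sociodemographic variables included as covariates". Arm effects are tested by Wald tests, and each of the two stepped-arm hypotheses is rejected at p below 0.025 after Bonferroni adjustment. The section also promises "CIs for ORs comparing the stepped arm with the low-intensity and high-intensity arms with coverage probabilities 0.975", by profile likelihood, with simultaneous coverage of at least 0.95.

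The Sample size considerations section uses a test level of 0.025 for two comparisons and the asymptotic normality of the log odds ratio. It therefore sides with the Analysis plan section. No part of the article ranks the two descriptions or calls the risk ratio supplementary.

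**The concern.** Both descriptions are current text, and both concern the one analysis on which the trial will be judged. They differ in effect measure, covariate adjustment, interval level and multiplicity control, and they are worded differently on facility and denominator. An abstract may leave detail out, but this one states different detail.

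Two things are at stake. First, retention is a common outcome here, so the odds ratio lies well away from the risk ratio, and a reader who expects one and is given the other will misjudge the effect. Second, a borderline result can be read as positive under the abstract and negative under the Analysis plan. The trial is non-blinded, so the choice between the two should not be left open until results are known.

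**Working it through.** **Inputs.** From Sample size considerations: retention of 40% (low), 60% (stepped) and 80% (high); 181 men per arm; 20% loss in every arm, counted as failure; level 0.025 per comparison; log odds ratio scale. Sidedness is not stated there; I take it as two-sided, which fits the 97.5% intervals. With losses as failures the rates become 0.8 × 0.40 = 0.32, 0.8 × 0.60 = 0.48 and 0.8 × 0.80 = 0.64.

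**1. Reproducing the stated power of 0.8.** Power = Φ(|log OR| / SE − 2.241), where SE² = 1/(n p₁q₁) + 1/(n p₂q₂) and 2.241 is the two-sided 0.025 critical value.
- Stepped v low: OR = (0.48/0.52)/(0.32/0.68) = 1.96, log OR = 0.674. SE² = 1/45.18 + 1/39.39 = 0.0475, SE = 0.218. Power = Φ(3.090 − 2.241) = 0.80.
- High v stepped: OR = (0.64/0.36)/(0.48/0.52) = 1.93, log OR = 0.655. SE² = 1/41.70 + 1/45.18 = 0.0461, SE = 0.215. Power = Φ(3.052 − 2.241) = 0.79.
- Low v high: power above 0.999, consistent with the stated 0.99.

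The sample size was therefore built on the Analysis plan's scale and level.

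**2. The same design on the abstract's scale.** SE² = q₁/(n p₁) + q₂/(n p₂) for the log risk ratio, keeping the 0.025 level.
- Stepped v low: RR = 0.48/0.32 = 1.50, log RR = 0.405, SE = 0.133, power = Φ(3.045 − 2.241) = 0.79.
- High v stepped: RR = 0.64/0.48 = 1.33, log RR = 0.288, SE = 0.095, power = Φ(3.017 − 2.241) = 0.78.

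**3. Effect size as reported (unadjusted).**

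| Comparison | Risk ratio | Odds ratio |
|---|---|---|
| Stepped v low | 1.50 | 1.96 |
| High v stepped | 1.33 | 1.93 |

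**4. One dataset, two readings.** Take 78/181 retained (stepped) against 58/181 (low), unadjusted, with Wald intervals.
- Abstract: RR = 78/58 = 1.34, log RR = 0.296, SE = 0.138. The 95% CI is exp(0.296 ± 1.960 × 0.138), or 1.03 to 1.76, which excludes 1.
- Analysis plan: OR = (78 × 123)/(58 × 103) = 1.61, log OR = 0.474, SE = 0.219. The 97.5% CI is exp(0.474 ± 2.241 × 0.219), or 0.98 to 2.62, with p = 0.030. This is not significant at 0.025.
- Cause of the difference: the risk ratio with a 97.5% interval is exp(0.296 ± 2.241 × 0.138), or 0.99 to 1.83, which also includes 1. The interval level reverses the reading here; the scale does not.

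**5. Familywise error.** With equal arms the two comparisons share the stepped arm, so their test statistics correlate 0.5 under the null. From the bivariate normal, the chance of at least one false rejection is 0.091 at 0.05 each (upper bound 0.10) and 0.047 at 0.025 each (upper bound 0.05).

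**The case against.** The detailed section and the sample size section agree, so the outlier is two sentences of an abstract, and a careful analyst would follow the detailed text. Odds ratio 1.96 and risk ratio 1.50 describe the same 48% against 32%. Unadjusted, both test the same null, and power differs by only about 0.01. This is right, and it limits the point to effect measure, covariate adjustment and interval level. It does not remove the conflict, because the abstract says what the primary analysis will be and no rule of precedence is given.

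Several stronger readings are tempting but are not supported.
- **That the trial's error rate is about 9%.** The abstract gives a p value but no threshold, and both detailed sections fix 0.025. A 95% interval can be reported alongside a test at 0.025. The 9% arises only if the 95% intervals decide.
- **That cluster-robust standard errors are specified and too small.** The abstract asks only that facility clustering be accounted for. A facility covariate, which the Analysis plan already has, is one way to do that. Any figure for inflation would describe an assumed software option.
- **That there are two usable denominators.** Study outcomes lists consent among eligible men as a process outcome, and Randomisation assigns arms only after enrolment and the baseline survey. Eligible men who decline have no arm and cannot be counted in one. The abstract's phrase is loose wording for randomised men.
- **That the cost-effectiveness analysis is affected.** Cost data already uses incremental numbers retained, which do not depend on the regression scale.
- **That the analyst is unblinded.** The article calls the trial non-blinded and says nothing about the analyst.

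**Conclusion.** The inconsistency is real and concerns the primary analysis. The abstract gives a risk ratio with a 95% interval and no multiplicity adjustment. The Analysis plan gives a covariate-adjusted odds ratio tested at 0.025 with a 97.5% interval, and the sample size supports the latter. At the planning rates the reported effect would be 1.50 or 1.96 (stepped v low) and 1.33 or 1.93 (high v stepped), depending on the text followed. Results with p between 0.025 and 0.05 would be read in opposite ways if the abstract's interval were taken as the criterion; familywise error would then be about 9% against the promised 5% at most. The figures are unadjusted and assume two-sided tests, 181 men per arm and losses counted as failures. The effect of covariate adjustment on the odds ratio is not quantified. The sample size itself is not in question, and the wording on facility and denominator needs tidying but does not amount to a rival analysis.

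**What to change.** Make the abstract match the Analysis plan and Sample size considerations sections: all randomised men, logistic regression with facility and the other stated covariates, tests at 0.025 for the two stepped-arm comparisons, and odds ratios with 97.5% intervals. This replaces the eligible-men denominator, the 95% interval and the separate clustering phrase.

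If a risk ratio is wanted for readability, it can be added as a supplementary standardised estimate from the same model, with a 97.5% interval. This is optional. If the risk ratio is in fact meant to be primary, the Analysis plan section must be rewritten instead, stating the link function, how facility is handled and 97.5% intervals, and power restated on that scale (about 0.79 and 0.78 with 181 per arm).

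The first option costs only wording, with no change to data collection or sample size. The 97.5% interval is about 14% wider than the 95% one on the log scale (2.241/1.960 = 1.14), which the Analysis plan already accepts. A standardised risk ratio would add a few lines of R.

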**Ethics and dissemination:**

The Institutional Review Board of the University of California, Los Angeles and the National Health Sciences Research Council in Malawi have approved the trial protocol. Findings will be disseminated rapidly in national and international forums and in peer-reviewed journals and are expected to provide urgently needed information to other countries and donors.

**Trial registration number:**

NCT05137210.

**Date and version:**

5 May 2023; version 3.

STRENGTHS AND LIMITATIONS OF THIS STUDYIdentifying efficient linkage strategies for men (IDEaL) provides male-specific differentiated models of care aimed to improve men’s antiretroviral therapy outcomes. We specifically focus on building trusting relationships with healthcare workers and developing client-led, individualised strategies to overcome barriers to care.IDEaL will test the impact of a stepped intervention for men. This approach promises to improve the efficiency and reach of HIV programmes for men as the highest-resource interventions will only be received by the minority of men who are most in need.IDEaL develops and tests a male-specific counselling curriculum that, if effective, could easily be taken to scale. Findings from the study will identify critical components for male-specific counselling, especially among men who struggle to be retained in HIV care.IDEaL interventions do not change facility characteristics that may act as barriers to men’s use of facility-based services. IDEaL focuses on providing outside-facility services for reaching men.

## Introduction

Men in sub-Saharan Africa (SSA) are under-represented in HIV programmes.^1^ Men are less likely than women to know their HIV status and to initiate antiretroviral therapy (ART), and more likely to face treatment interruptions once in care.^2^ Only 69% of men who start ART reach viral suppression compared with 77% of women.^2^ As a result, men in the region are 37% more likely to die from AIDS-related causes as compared with women.^3^

One contributor to men’s poor HIV outcomes is an increased risk of disengagement from care. Engagement in ART programmes is not static—many ART clients cycle through care, starting and stopping HIV care multiple times throughout their lifetime.^4 5^ Up to 46% of ART clients experience treatment interruption,^6–8^ and between 30% and 40% of those who return experience repeat treatment interruption within 6 months.^9 10^ Men are particularly prone to cycling through ART programmes, with more frequent stop–start instances and longer periods outside of care as compared with women.^6 11–13^ Improving men’s long-term engagement in HIV care is critical for men’s health and reducing HIV transmission.^14^

Men who disengage from HIV programmes (either after testing HIV positive or after enrolling in HIV care services) are frequently described as a difficult and ‘hard-to-reach’ population.^15 16^ However, growing evidence suggests that men desire HIV services^17 18^ but encounter multiple health systems barriers to care that make it impossible to stay in long-term care.^19^ There is an urgent need to develop client-centred strategies tailored to men that facilitate men’s engagement and re-engagement in HIV treatment programmes.

Some men may require male-specific interventions to facilitate engagement in HIV care. Men have less exposure to HIV services than women^19 20^ and work demands may conflict with ART clinic schedules.^21 22^ Difficult interactions with healthcare workers (HCWs) can also prevent men from engaging or re-engaging in care.^23 24^ Furthermore, most ART counselling curricula do not target men and often lack the client-centred counselling needed to develop internal motivation to engage and stay engaged in care.

Differentiated service delivery (DSD) models are now being developed to improve men’s ART engagement throughout SSA.^25–27^ As DSD models for men are developed, it is critical that strategies be feasible and cost-effective to allow scale-up. A ‘one-size-fits-all’ model is not as effective as more nuanced approaches.^28–30^ Stepped interventions increase in intensity over time and are purposively designed to address prevailing barriers in the target population in order to positively affect the desired outcome.^31 32^ An incremental, stepped approach may be the most appropriate and scalable way to improve men’s care in low-resource settings. Men are not homogeneous: some men may require minimal support to engage in care, while others may require extensive support. Stepped interventions allow programmes to target the highest-resource interventions to the minority of men who need them most.

The *Identifying efficient linkage strategies for men (IDEaL) trial* is an individually randomised control trial aimed to test the impact of various interventions on ART (re)initiation and 6-month retention among men living with HIV who are not currently engaged in HIV care in Malawi. We will compare a stepped intervention against low-intensity and high-intensity interventions to assess the impact of the stepped intervention on men’s use of ART services over time (see online supplemental file 1). The trial contributes to existing literature by testing male-specific, client-centred strategies to re-engage men in care. This is one of the first trials specifically designed with men’s re-engagement in care in mind. If effective, such interventions may decrease repeat treatment interruption and duration of treatment interruptions among men, which can improve viral suppression and reduce onward HIV transmission.^14^

10.1136/bmjopen-2022-070896.supp1Supplementary data

## Methods and analysis

### Objectives

Our primary objective is to test the effect of a male-specific, stepped intervention on men’s 6-month retention in ART care compared with male-specific low-intensity and high-intensity interventions (retention is defined as <28 days late for their 6-month ART appointment). Secondary objectives are to understand the effect of a stepped intervention on: (1) ART initiation; (2) the presence of adverse events (ie, unwanted disclosure, end of relationship or intimate partner violence (IPV)); (3) intervention acceptability and (4) cost-effectiveness.

### Trial design

IDEaL is a programmatic, individually randomised, non-blinded controlled trial design. We will recruit men from 13 high-burden health facilities in Malawi using medical chart reviews to identify men who are living with HIV but not engaged in HIV care.

### Randomisation

Individual men will be block randomised using R by a biostatistician using a 1:1:1 ratio to either the stepped, low-intensity or high-intensity study arm using a computer-generated program. Participants will be randomised in blocks of 3 and 6, depending on the number of men available for recruitment at each facility. After enrolling in the trial and completing a baseline survey, men will be assigned to a study ID based on the randomisation list. Study IDs will be linked with the preassigned blocked randomisation and preloaded into the tablet device, but will be unknown to the study staff until survey and randomisation modules are completed and saved, ensuring randomisation cannot be manipulated by the study staff. Once finalised, the randomisation results will appear on the tablet device as a picture, and will be shown to the participant to maximise transparency and study buy-in.

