### Data collection

Study recruitment, enrolment and data collection will be conducted by male study staff, who are distinct from local HCWs implementing the interventions.

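### Blocks of 3 and 6, set by facility supply in an open-label trial, leave some allocations foreseeable; the tablet procedure guards against tampering, not against prediction

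*Protocol article*

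**What the plan says.** Under Randomisation, the protocol article sets allocation "using a 1:1:1 ratio to either the stepped, low-intensity or high-intensity study arm" and fixes the blocks: "Participants will be randomised in blocks of 3 and 6, depending on the number of men available for recruitment at each facility". It does not say that sizes vary at random or that they are withheld from recruiters.

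The safeguard in the same section is that study IDs, already tied to the list, sit on the tablet and "will be unknown to the study staff until survey and randomisation modules are completed and saved". The article concludes that this has the effect of "ensuring randomisation cannot be manipulated by the study staff". Once saved, "the randomisation results will appear on the tablet device as a picture, and will be shown to the participant".

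Three other statements bear on the point:

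- Trial design: "IDEaL is a programmatic, individually randomised, non-blinded controlled trial design", and "We will recruit men from 13 high-burden health facilities in Malawi".
- Data collection: "Study recruitment, enrolment and data collection will be conducted by male study staff". These staff are separate from the health workers who deliver the interventions.
- Tracing and eligibility screening: study staff trace the men found in chart reviews, by phone or home visit, with up to three attempts.

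**The concern.** In a permuted block, the closing allocations follow from the earlier ones. Anyone who has seen the earlier results and knows the block size knows the last arm before the next man is approached. Concealing the ID until the survey is saved does not help, because the information lies in the past allocations and not in the hidden one.

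The people who see those results also trace, screen and enrol, so they have some say over whom to pursue next and in what order. If a foreseen arm influenced that choice, knowingly or not, the arms could differ in motivation to return to care, which is closely tied to 6-month retention. Covariate adjustment would deal with such a difference only in part.

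**Working it through.** **Inputs from the article.** Three arms at 1:1:1; blocks of 3 and 6 (Randomisation); 181 men per arm, 3 × 181 = 543 (Sample size considerations); 13 facilities (Trial design), so 543 / 13 ≈ 42 men per facility on average.

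**The plan's own figure.** The article gives no predictability figure. The design figure that can be reproduced is the power of 0.8. With 20% loss counted as failure, the assumed 40/60/80% become 32/48/64%. Using a Wald test on the log OR, two-sided level 0.025 (critical value 2.241), 181 per arm:

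- Stepped v low: log OR = 0.674; SE = √[1/(181 × 0.32 × 0.68) + 1/(181 × 0.48 × 0.52)] = 0.218; power = Φ(3.090 − 2.241) = 0.802.
- Stepped v high: log OR = 0.655; SE = 0.215; power = Φ(3.052 − 2.241) = 0.791.

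Both agree with 0.8. The sample size is not in dispute.

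**Case A: one sequence per facility, block size known, all earlier allocations there seen.**

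*Block of 3.* Slot 3 is always determined: 1/3 = 33.3%. The best guess is right (1/3 + 1/2 + 1)/3 = 61.1% of the time.

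*Block of 6.* Slot 6 is always determined. Slot 5 is determined when the two remaining places belong to the same arm: 3 of the 15 possible pairs, or 1/5. Share determined = (1 + 1/5)/6 = 20.0%. The chances of a correct best guess in slots 1 to 6 are 1/3, 2/5, 1/2, 8/15, 3/5 and 1; their mean is 56.1%.

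Full enumeration of the blocks gives the same values. Over 543 men: 543 × 0.20 ≈ 109 and 543 / 3 = 181.

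**Case B: one sequence per facility, sizes 3 and 6 mixed at random, next size unknown.** This is a simulation of 42 men per facility. The observer knows only that sizes are 3 or 6 and in what proportion, and updates on every earlier allocation.

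| Share of blocks of size 3 | Fully determined | Best guess right |
|---|---|---|
| 25% | 10.9% | 56.4% |
| 50% | 8.4% | 57.4% |
| 75% | 5.1% | 59.0% |

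On 543 men, 5% to 11% is about 27 to 60. In the last row only 5.1% are certain, but 27.7% can be called with more than 90% probability, so the share that is certain understates what a careful observer could infer.

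**Case C: a larger scheme for comparison.** Sizes 6, 9 and 12 drawn at random with equal probability and unknown to staff, same simulation: about 2.4% determined, best guess right about 52%.

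Chance accuracy is 33.3% throughout.

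**The case against.** The strongest reply is that the 20% to 33% range rests on conditions the article does not state outright: a separate sequence per facility, one size throughout a facility, recruiters who know that size, and recruiters who see every earlier allocation there. The text would also allow both sizes within one facility, and publication of the sizes does not show that recruiters were told them. This stands, and it is why Case B belongs beside Case A. It does not remove the point. The article names facility supply as what sets block size, which points away from random mixing, and a best guess in Case B is still right 56% to 59% of the time.

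Second, the assurance closes a sentence about preloaded, hidden IDs, and against look-up and alteration that procedure works: a man is enrolled and surveyed before his arm appears. This also stands. A reader might infer that the assurance is simply false. The documents do not support that; its wording is only wider than the protection described.

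Third, opportunity and motive are limited. The men are hard to find, all three arms are active, and recruiters do not deliver the interventions. This lowers the risk, but some discretion over tracing order and outpatient screening remains.

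Fourth, a reader might infer bias that no analysis can remove. That is too absolute: the Analysis plan adjusts for age, marital status, facility and other sociodemographic variables, and the baseline survey records previous use of HIV services. Selection on measured factors can be partly adjusted for; selection on unmeasured motivation cannot.

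**Conclusion.** The point holds in conditional form. With a known or inferable block size and a separate sequence per facility, 20% to 33% of allocations (about 109 to 181 of 543) are foreseeable. With sizes mixed at random and unknown to staff, about 5% to 11% (roughly 27 to 60) are determined. Both cases assume recruiters see the earlier allocations at their facility; a single sequence across all 13 facilities, or lists split between tablets, would make prediction harder.

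A reader might go further and put a size on the bias. If every foreseeable slot in one arm went to men 20 percentage points likelier to be retained, that arm would shift by 0.20 × 20 = 4 to 0.333 × 20 ≈ 7 points, against planned differences of 16 (after loss) to 20. That is an extreme case: it needs every such slot recognised and used in the same direction at all facilities. Nothing in the article indicates that this would happen. Predictability is a risk of selection bias, not proof of it.

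**What to change.** **If any enrolment remains:** generate facility-stratified lists with block sizes drawn at random from larger multiples of 3 (for example 6, 9 and 12), not set by the number of men available, and withhold sizes and order from recruiting staff. The work is to regenerate the lists and reload the tablets. The statistical cost is a largest possible between-arm difference of 4 men per facility when recruitment stops (an incomplete block of 12), instead of 1 (block of 3) or 2 (block of 6), among about 42 men; the planned facility covariate handles this. The gain is largest if sizes are now fixed and known. If they are already mixed and hidden it is modest: at a 50:50 mix, best-guess accuracy falls from about 57% to 52% and determined slots from about 8% to 2.4%.

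**In either case:** limit the assurance to look-up and alteration of assignments, and state whether each facility has its own sequence, whether sizes vary at random and whether recruiters know them.

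**If enrolment is complete:** make those wording changes and report the block scheme as a limitation. This costs only text.
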